### Dissemination

The study results will be presentated at medical and scientific conferences and published in a peer-reviewed clinical journal. The results of this study will also help meet the requirements of research higher degree completions. Participants will receive a lay summary of the study results.

### Participant withdrawals

A participant may withdraw from the study at any time. All data that has been collected from the participant up until the point of withdrawal will be included in the final analyses (unless withdrawal occurs prior to randomisation). Participants that are lost-to-follow-up, decline to complete testing (due to perceived incapacity, injury, or changes in personal circumstances), or who are deceased will not be deemed as withdrawals from the study and all data collected from these participants will be included in the final analyses.

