The primary outcomes for assessing the efficacy of the intervention on cardiovascular health will be change in VO_2_peak assessed via cardiopulmonary exercise testing and peak cardiac output assessed via exercise cardiac magnetic resonance imaging (ExCMR) (multiple primary outcomes). Secondary outcomes will include prevalence of functional independence (VO_2_peak ≥ 18 mL.kg^−1^.min^−1^) as well as patient reported fatigue and quality of life. Exploratory outcome measures will include changes in cardiac reserve, indices of resting cardiac structure and function (cardiac mass, myocardial fibrosis, diastolic and systolic function), central vascular compliance, cardiovascular biomarkers (troponin-I [cTn-I], brain natriuretic peptide [BNP], glycaemic control, lipid profile and adiposity), skeletal muscle structure and function (lean body mass, thigh muscle cross-sectional area and fat fraction, oxygen uptake kinetics, and muscular strength, power and stability) as well as anxiety, depression and transplant related outcomes including engraftment indices (time to neutrophil and platelet engraftment, immune reconstitution) and development of GVHD. The study will also assess habitual physical activity and dietary intake due to their potential impact on cardiovascular outcome measures. An overview of the protocol assessments and outcomes can be seen in Fig. 2.

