### Sample size calculation

No prior studies have directly assessed the effect of a structured exercise intervention on changes in VO_2_peak and cardiac output in this patient cohort. As such, we based our sample size calculations on data collected from our group’s previously published work that utilised a similar exercise intervention in women being treated for breast cancer [74], whereby clinically meaningful changes in cardiorespiratory fitness and cardiac function were observed. The present study is powered to detect a minimum between-group difference in VO_2_peak of 10% (SD = 11%, effect size = 0.91) and cardiac output of 9% (SD = 10%, effect size = 0.9) after treatment, assuming a conservative correlation coefficient of *r* = 0.4 between baseline and follow-up testing. To detect this difference 20 completions per group are required (80% power; alpha = 0.025; multiple primary endpoints). To account for withdrawals, mortality associated with disease progression and treatment, and uncertainty related to the COVID-19 pandemic, a total of 60 participants will be recruited (Ex + SED; *n* = 30 and UC; *n* = 30).

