### Statistical analyses

To examine the differential effects of the intervention on VO_2_peak, peak cardiac output, and additional secondary and exploratory outcome measures, generalised linear mixed modelling will be conducted (adjusted for baseline values) with participants as the random effect, time as the repeated measures factor, and group and group-by-time interactions as the fixed effects. The covariance structure of the model will be informed by the Akaike information criteria. The primary analysis will be conducted on an intention-to-treat basis and a probability level of 0.025 will be adopted to account for multiple primary outcome endpoints. Standardised effect sizes (Cohen’s *d*) will be calculated to determine the magnitude of change for within and between group effects. A per protocol analysis including participants who completed > 66% of the planned exercise sessions will also be performed.

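### The per-protocol rule selects on health in the exercise arm only, and the functional-independence comparison covers only participants who survive and can be tested

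*Protocol article*

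**What the plan says.** **Per-protocol set.** The primary analysis is a baseline-adjusted mixed model by intention-to-treat. The Statistical analyses section then adds: "A per protocol analysis including participants who completed > 66% of the planned exercise sessions will also be performed". No criterion is given for usual care, whose participants wear a tracker and are visited but get no exercise support (Usual care control group).

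The section on safety precautions lists absolute contraindications to exercise, among them fever, low platelets and low haemoglobin. The section on adherence and attendance records clinical contraindication as one reason for a missed supervised session.

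**Functional independence.** The text below Table 3 says "Secondary outcomes will include prevalence of functional independence", defined as VO2peak of at least 18 mL/kg/min. Table 3 schedules the cardiopulmonary exercise test (CPET) at baseline and 12 weeks after discharge, and not at the post-inpatient visit.

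**Participants without a 12-week test.** Under Participant withdrawals, those who are lost, who decline testing (perceived incapacity is one listed reason) "or who are deceased will not be deemed as withdrawals from the study and all data collected from these participants will be included". The Experimental protocol section commits to testing, where possible, participants who do not adhere or who stop the intervention. The Sample size calculation raises recruitment to 30 per arm "To account for withdrawals, mortality associated with disease progression and treatment", and also for pandemic uncertainty.

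**The concern.** Only one arm has planned sessions, so the attendance rule can filter only that arm. Read literally, it admits no usual-care participant at all; the only reading that yields a between-group comparison sets exercisers who pass against all of usual care. The protocol itself links the filter to the outcome: low haemoglobin bars exercise, and the Background names the haematological part of oxygen transport as contributing to VO2peak decline. Part of any apparent benefit in this analysis could therefore be selection.

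For functional independence, including all collected data is nominal. With one follow-up CPET, a participant who dies or cannot be tested has only a baseline value, which carries essentially no information on the 12-week effect. The document assigns these participants no outcome, although some are among the clearest cases of not being independent. The reported prevalence then describes tested survivors, and the contrast between arms depends on who reached the test.

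**Working it through.** **1. The plan's own figure.** The plan says "20 completions per group are required (80% power; alpha = 0.025; multiple primary endpoints". Inputs: "SD = 11%, effect size = 0.91" for a 10% difference in VO2peak; "cardiac output of 9% (SD = 10%, effect size = 0.9"; and a baseline to follow-up correlation of 0.4. With two-sided alpha 0.025 (sidedness is not stated), n per arm = 2(2.241 + 0.842)² / d² × (1 − 0.4²).

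- VO2peak: 23.0 × 0.84 = 19.3, rounded up to 20.
- Cardiac output: 23.5 × 0.84 = 19.7, rounded up to 20.

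The figure reproduces and is not in dispute. It allows 1 − 20/30 = 33% of each arm to lack the 12-week outcome.

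**2. Per-protocol shift with no true effect.** Take attendance and outcome as jointly normal with correlation ρ arising through health alone, and let a share q of the exercise arm pass. The mean of the top share q of a standard normal is φ(z)/q, where z is the cut-off that a share q exceeds. Shift = SD × ρ × φ(z)/q, with SD 11% from the plan. Both q and ρ are assumptions; the document gives neither.

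| Share passing | φ(z)/q | ρ = 0.2 | ρ = 0.3 | ρ = 0.5 |
|---|---|---|---|---|
| 80% | 0.350 | 0.8 | 1.2 | 1.9 |
| 65% | 0.570 | 1.3 | 1.9 | 3.1 |
| 50% | 0.798 | 1.8 | 2.6 | 4.4 |

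Entries are percentage points of VO2peak towards exercise. At 65% passing, 0.570 × 0.2 to 0.5 is 0.11 to 0.29 SD. At ρ = 0 the shift is zero.

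A simulation (20,000 replicates, 20 per arm before filtering, unadjusted t-test at 0.025) agrees with these shifts. At ρ = 0.5 it gives false-positive rates of 4.2%, 6.8% and 9.9% for 80%, 65% and 50% passing. At ρ = 0.3 they are 3.1%, 4.0% and 4.9%.

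**3. Functional independence with no true effect.** Assume 30 per arm and 47% independent among all randomised, so 0.47 × 30 = 14.1 per arm. The 47% is 1 minus the 53% disability figure in the Background, which is an upper figure for survivors and serves only as illustration. Tested-only prevalence = (14.1 − independent among the lost) / number tested.

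| Lost, exercise v usual care | Share of lost not independent | Exercise | Usual care | Difference, points |
|---|---|---|---|---|
| 10 v 10 | 100% | 14.1/20 = 70.5% | 70.5% | 0 |
| 10 v 6 | 100% | 70.5% | 14.1/24 = 58.8% | +11.7 |
| 10 v 6 | 75% | 11.6/20 = 58.0% | 12.6/24 = 52.5% | +5.5 |
| 10 v 6 | 50% | 9.1/20 = 45.5% | 11.1/24 = 46.2% | −0.8 |

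Swapping the losses between arms reverses each sign. Where all the lost are not independent, counting them so restores 14.1/30 = 47% in both arms.

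**The case against.** **On the per-protocol rule.** It defines an additional analysis; intention-to-treat is primary. The shift depends on assumed values, baseline adjustment may absorb part of it, and even 3.1 points is under a third of the design difference. Illness does not always cost a session: relative contraindications limit intensity instead. All of this stands, and it keeps the point modest. It does not make the comparison a randomised one.

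A complier-average estimate cut at 66% might look like the natural replacement. It would assume no benefit below the cut-off, yet lower attenders still train and the whole exercise arm is prompted to take sedentary breaks. With 65% passing it multiplies the intention-to-treat effect by 1/0.65 = 1.54, crediting the attenders with benefit that others gained.

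**On functional independence.** Three stronger readings are tempting.

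- A reader might infer that the plan excludes the dead or untestable. It says the reverse; they drop out in effect, because the single follow-up value is absent.
- A reader might infer that the between-arm difference is biased. That needs health-related loss to differ by arm, and the document does not show that it will. Differential loss is conceivable, since exercisers train twice weekly at the testing site, but the direction is unknown and testing is to be attempted in everyone where possible.
- A reader might compute 0.47 × 20/30 = 31% and call it the true prevalence. That scores all ten losses per arm as not independent, although the allowance also covers withdrawals and the pandemic.

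Imputation and missing-data sensitivity methods may sit in an analysis plan that is not shown, and their absence here is no fault. Prevalence among tested survivors is also a legitimate quantity, if it is labelled as such.

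**Conclusion.** The per-protocol half holds. The stated rule filters one arm on a criterion tied to health, so the comparison is non-randomised and probably favours exercise: by about 1.3 to 3.1 points of VO2peak if 65% pass and the correlation is 0.2 to 0.5, and by nothing if attendance is unrelated to outcome. The intention-to-treat analysis is not touched by this rule.

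The functional-independence half holds in a narrower form. The comparison covers tested survivors. Equal and similarly selected loss raises both prevalences without moving the difference. Loss of 10 v 6 could move it by about 5.5 to 11.7 points in either direction if 75% to 100% of the lost are not independent. The loss counts and shares are assumptions. The documents do not support the claim that both results are biased.

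**What to change.** **Per protocol.** Keep intention-to-treat as the basis for conclusions. Label the per-protocol comparison non-randomised and supportive. Beside it or in its place, report an instrumental-variable estimate with randomisation as the instrument and the proportion of planned sessions attended as the exposure (zero in usual care), rather than a 66% cut-off. Attendance is already recorded. Cost: a wider interval, an assumed linear relation between attendance and benefit, and an exclusion assumption that the sedentary-break component may strain. This estimate does not repair missing CPETs.

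**Functional independence.** Record why each 12-week CPET was not done, separating death and medical inability from other reasons. Add an analysis of all randomised participants that counts death or medical inability to test as not independent, and report it beside the tested-only prevalence, labelled as applying to tested survivors. Cost: one extra data field and a few lines of analysis text. The composite mixes death with low fitness, so the two results should be read together. Recruitment was still open when the article was submitted; both rules should be fixed before outcome data are examined by arm.

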## Discussion

Allo-SCT survivors experience elevated rates of premature cardiovascular disease [6, 13–18], functional impairment and poor quality of life [9, 11, 12, 75]. Mounting evidence from observational studies indicates these cardiovascular impairments are apparent within the early stages of the transplant process [11, 12], suggesting that this may be an opportune time to intervene and mitigate these consequences. Exercise interventions have been shown to prevent functional decline in oncology populations and may also be an efficacious primary preventative approach for allo-SCT patients [76]. This study will comprehensively evaluate the efficacy of intervening early in the transplant process with a multi-faceted exercise intervention in mitigating the detrimental effects associated with allo-SCT.

Currently, the utility of exercise as a potential therapeutic strategy to counteract the detrimental cardiovascular consequences associated with allo-SCT is not well characterized. While previous studies have demonstrated a beneficial effect of exercise on functional capacity in allo-SCT recipients [11, 31, 33, 35–39], these studies have varied significantly in the type, timing and duration of intervention delivered, as well as the cardiovascular endpoints assessed. Indeed, in contrast to previous studies, the ALLO-Active trial will incorporate strategies to not only increase purposeful aerobic and resistance exercise but also reduce and break-up sedentary time through replacement with light-intensity exercise. This novel multi-faceted exercise approach—which was informed by evidence that prolonged sedentary behaviour poses a detrimental risk to cardiovascular health independent of physical activity levels [43, 44]—has the potential to benefit cardiovascular outcomes in allo-SCT recipients. Specifically, we hypothesise that this will occur through a combination of systemic and molecular mechanisms that act to oppose the negative effects of physical deconditioning, cancer therapies and allografting on metabolic and growth signalling pathways in the heart and periphery. Furthermore, the ALLO-Active intervention will be delivered during allo-SCT and acute inpatient recovery (~ 4 weeks) and for 12 weeks post-discharge (~ 16 weeks total). This timing is designed to prevent the cardiovascular consequences as they occur throughout the transplant process. While some studies have intervened at this early stage [11, 31, 32, 35, 77], the absence of comprehensive cardiovascular evaluation and insufficient intervention durations (4–10 weeks) mean that conclusive evidence supporting the therapeutic utility of exercise and sedentary behaviour reduction (through replacement with light exercise) as a primary preventative strategy is still required. Indeed, the ALLO-Active trial will be the first to quantify the efficacy of a multi-faceted exercise intervention (exercise combined with interruption in sedentary time) in preserving directly measured VO_2_peak (via gold standard cardiopulmonary exercise testing). VO_2_peak encapsulates the integrative functioning of the cardiovascular, hematological, and skeletal muscle systems, has proven prognostic utility for predicting cardiovascular risk and outcomes, and therefore, is likely to be sensitive to the beneficial effects of the intervention. The ALLO-Active trial will also be the first to comprehensively characterise the effect of an exercise and sedentary behaviour intervention on the cardiac, vascular, hematological, and skeletal muscle factors that underlie changes in VO_2_peak and cardiovascular risk following allo-SCT. This will include novel resting echocardiographic and ExCMR imaging methods, as well as aortic and thigh MRI which are sensitive to subclinical changes in cardiac, vascular, and skeletal muscle, respectively. Taken together, this trial will provide important information regarding the efficacy of exercise in counteracting the multiple cardiovascular insults imposed by allo-SCT.

### Practical implications

Currently, guidelines for patients undergoing cancer treatment and for cancer survivors support the incorporation of exercise as a part of standard care and recommend adherence to typical physical activity and sedentary behaviour guidelines for the general population [78, 79]. Exercise has been shown to be safe and effective for reducing the burden of many adverse physical and psychological effects associated with cancer treatment [80–83]. However, optimising the type and timing of specific exercise interventions in allo-SCT patients requires further investigation. In this regard, the outcomes from this study will help to inform future evidence-based guidelines for allo-SCT patients for clinicians and provide insight regarding the efficacy of an exercise intervention for mitigating the detrimental cardiovascular effects and reductions in quality of life associated with the treatment. The feasibility and adherence to the intervention will be evaluated once the study has been completed to assist with the design of future, larger cohort, and multicentre studies.

### Practical challenges, strengths, and limitations

There are challenges associated with conducting this type of intervention within a clinical cohort that commonly experience a wide range of treatment-related adverse effects. From a practical perspective, the ability of the patients to perform the intervention in accordance with the study protocol may be impacted by the erratic health status of the individuals throughout their treatment. Indeed, in this acute setting, it is common for allo-SCT patients to report high levels of nausea, fatigue, breathlessness, muscle pain, diarrhea, and loss of appetite, amongst many other side effects [84]. Furthermore, low hemoglobin and platelet levels are inherent to allo-SCT and can persist throughout acute inpatient and outpatient recovery. As such, all exercise sessions will be individualised to accommodate each participant’s current health status. For instance, both objective (heart rate and workload) and subjective (RPE) measures of intensity will be assessed to accommodate any daily fluctuations in physiological presentation.

Despite these challenges, the study has several strengths. These include gold standard CPET assessments of VO_2_peak combined with comprehensive cardiovascular and peripheral imaging techniques, which will provide a detailed characterisation of the effect of allo-SCT (and therapeutic benefit of the intervention) on VO_2_peak and the determinants underlying changes in VO_2_peak and cardiovascular risk in this population. Moreover, this type of intervention which has low barriers for initiation and high potential for continuation may be particularly accessible in this cohort. Limitations associated with our study design including participant recruitment from a single site and a relatively small sample size. The nature of a study involving an exercise intervention may also be biased towards the recruitment of participants who are already physically active; therefore, the usual care group may reflect a population more motivated and physically active than typically observed in this cohort. The lack of blinding for the assignment of a participant’s study group, although unavoidable, may also be considered a study limitation.

In summary, the ALLO-Active study will be the first randomised, controlled trial to examine the efficacy of intervening early with a multi-faceted exercise program to preserve cardiovascular function in allo-SCT recipients. The primary outcomes will focus on changes in VO_2_peak and peak cardiac function, while the secondary aims will evaluate the efficacy of the intervention to improve quality of life, and reduce fatigue and prevalence of functional disability (VO_2_peak < 18 ml.kg^−1^.min^−1^). The outcomes of this study will assist with the development of evidence-based guidelines for recommending exercise as an adjunct therapy throughout allo-SCT.

### Trial status

At the time of submission, participants are currently being recruited and enrolled.

## Data Availability

The datasets used and/or analysed during the current study are available from the corresponding author on reasonable request.

## Abbreviations

ACSM: American College of Sports Medicine
Allo-SCT: Allogeneic stem cell transplant
AT: Aerobic training
BHDI: Baker Heart and Diabetes Institute
BNP: Brain natriuretic peptide
BSA: Body surface area
CI: Cardiac index
CMR: Cardiac magnetic resonance imaging
CPET: Cardiopulmonary exercise test
cTn-I: Troponin-I
CVD: Cardiovascular disease
DXA: Dual energy X-ray Absorptiometry
EDV: End-diastolic volume
ESV: End-systolic volume
Ex + SED: Exercise and sedentary behaviour intervention
ExCMR: Exercise cardiac magnetic resonance imaging
FACIT-Fatigue: Functional Assessment of Chronic Illness Therapy – Fatigue subscale
FACT-BMT: Functional Assessment of Cancer Therapy with Bone Marrow Transplant
GLS: Global longitudinal strain
HADS: Hospital Anxiety and Depression Scale
HR: Heart rate
HR_peak_: Heart rate peak
LV: Left ventricular
LVEF: Left ventricular ejection fraction
MET: Metabolic equivalent of task
MRI: Magnetic resonance imaging
RER: Respiratory exchange ratio
RPE: Rating of perceived exertion
RT: Resistance training
RV: Right ventricular
RVEF: Right ventricular ejection fraction
SPPB: Short physical performance battery
SSFP: Steady-state free precession
SVI: Stroke volume index
UC: Usual Care
VCO_2_: Volume of carbon dioxide production
V_E_/VCO_2_ slope: Minute ventilation to carbon dioxide production slope
V_E_: Minute ventilation
VO_2peak_: Volume of peak oxygen consumption
VT: Ventilatory threshold
